### Recruitment {15}

All women attending their routine second trimester ultrasound scan (19.0 23.6 weeks of gestation) will be invited to fill an eligibility questionnaire with a list of risk factors based on the criteria established by the RCOG [38]. The investigators involved in the recruitment will revise the inclusion/exclusion criteria and will address eligible patients about the purpose of the study and the voluntary nature of the participation. Women who agree to participate, after obtaining written informed consent, will be randomized and assigned a randomization code. Randomization will be performed using a web-based system which randomly assigns participants to one of the three different arms of intervention: (1) nutrition program based on MedDiet; (2) stress reduction program based on mindfulness techniques, MBSR; and (3) usual care without any intervention.

### Assignment of interventions: allocation

#### Sequence generation {16a}

The computer-generated randomization sequence is based on restricted randomization, with a forced strict number of participants per branch at the end of the trial. It is protected and managed by a computer technician of the foundation “*Medicina Fetal Barcelona*” which has no role in recruitment. The investigators enter data of the patient that is recruited on a website, and the computer generates automatically the inclusion number and treatment assignment. Participants are randomly assigned to either usual care, MedDiet, or MBSR with a 1:1:1 allocation as per computerized random number generator, with equal proportion in each group. An additional code is also generated, so the patient can have access to the official website of the study to a specific part according to her intervention (https://fetalmedbarcelona.org/impactbcn/).

#### Concealment mechanism {16b}

Participants are randomized using an online central randomization service. Allocation concealment is ensured, as the service does not release the randomization code until the patient has been recruited into the trial, which takes place after eligibility has been confirmed and the consent form signed.

The inclusion number of the patient and the treatment assignment will be printed and saved in the investigator’s files. A copy will be given to the patient.

#### Implementation {16c}

All participants who give consent for participation and who fulfill the inclusion criteria are enrolled and randomized. Randomization is requested by the investigator responsible for the recruitment. A different investigator, responsible for the allocation, generates the allocation sequence using an online central randomization service. The investigator responsible for the allocation finds out the study arm and gives the information about intervention allocation to the participant. The staff responsible for the recruitment is not allowed to receive information about the group allocation.

The enrollment of the participants and the follow-up of the trial will be done by doctors and research assistants of BCNatal.

The nutrition intervention will be conducted by two expert dieticians and supervised by the Research Group on Nutrition, Cardiovascular Disease and Aging from IDIBAPS - Hospital Clinic of Barcelona ([name]), with huge experience in this field of research [18].

The mindfulness intervention based on the MBSR program will be coordinated by co-founders of the *Institute of Mindfulness*, with instructors certified by the Center of Mindfulness in Medicine, Health Care and Society, University of Massachusetts Medical School, Worcester, MA, USA. The program has been supervised by the head of the Psychiatry Service of Hospital Clinic de Barcelona ([name]).

### Assignment of interventions: blinding

#### Who will be blinded {17a}

Due to the nature of the intervention, it is not possible to blind participants or researchers involved in the trial with respect to the study group.

#### Procedure for unblinding if needed {17b}

Not applicable, and the trial will be not blinded.

### Data collection and management

#### Plans for assessment and collection of outcomes {18a}

At the moment of enrollment (19.0–23.6 weeks of gestation), lifestyle questionnaires *(State-trait Anxiety Inventory-STAI* [45], *Perceived Stress Scale* [46], *WHO Five Well Being Index* [47], *Five Facet Mindfulness Questionnaire-FFMQ* [48], *Pittsburgh Sleep Quality Index-PSQI* [49]), a visit with a dietitian for a nutritional assessment (*Food Frequency Questionnaires-FFQ*, *MedDiet Adherence* without the inclusion of alcohol, *Minnesota Physical Activity*, all used in previous studies [18]), and biological samples (maternal hair, peripheral blood, urine, vaginal and fecal swaps) will be taken from each woman. Participants will be scheduled for a final visit with also a detailed ultrasound assessment (fetal biometry and Doppler, fetal echocardiography, fetal neurosonography) at the end of the interventions (34.0–36.6 weeks of gestation): the same lifestyle questionnaires, another visit with a dietitian for a nutritional assessment, and the same biological samples (maternal hair, peripheral blood, urine, vaginal and fecal swaps) will be taken again. Additionally, a subgroup of women will be randomly selected for a magnetic resonance of the maternal brain, fetal brain, and placenta. Maternal and feto-placental biological samples (cord blood and placenta) will be taken at birth. Perinatal outcomes will be recorded within 28 days after delivery. Postnatal follow-up consists of several visits at different ages of the assessment of neurological functions with neurodevelopmental tests, the assessment of cardiovascular functions (blood pressure, heart rate), and biological samples (fecal swaps for microbiota evaluation). Visits are scheduled at 1–3 months (*Neonatal Behavioral Assessment Scale-NBAS* [50]), at 12 months (*Ages and Stages Questionnaires-ASQ* [51]), and at 2 years of corrected age (*Bayley Third edition* [52]).

Maternal and fetal biological samples will be analyzed to assess compliance. Additional analysis will include biomarkers for maternal nutrition (vitamins, iron, folate, cholesterol, and lipid levels), metabolomics, epigenetics, and gut and vaginal microbiota.

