**Methods:**

A randomized parallel, open-blind, single-center trial following a 1:1:1 ratio will select and randomize high-risk singleton pregnancies for FGR (*N*=1218), according to the criteria of the Royal College of Obstetricians and Gynaecologists (19.0–23.6 weeks’ gestation), into three arms: Mediterranean diet, mindfulness-based stress reduction program, and usual care without any intervention. Compliance to the interventions will be randomly tested in 30% of participants with specific biomarkers. Maternal socio-demographic, clinical data, biological samples, and lifestyle questionnaires will be collected at enrollment and at the end of the interventions (34.0–36.6 weeks’ gestation), together with a fetoplacental ultrasound and magnetic resonance. Fetoplacental biological samples and perinatal outcomes will be recorded at delivery. Postnatal follow-up is planned up to 2 years of corrected age including neurodevelopmental tests and cardiovascular assessment. Intention-to-treat and population per-protocol analysis will be performed.

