#### Strategies to improve adherence to interventions {11c}

##### Participant compliance

Adherence to the nutritional intervention will be assessed by an improvement adherence to the MedDiet, based on an improvement of ≥3 points of their total final score of the 17-item dietary screener compared to their total initial score. The study population will be described according to adherence to the MedDiet, depending on the score: ≥12 high adherence, 6–11 moderate adherence, and <6 low adherence.

Adherence to the MBSR program will be assessed by class attendance and time spent engaged in mindfulness meditation outside of class sessions. The treatment will be considered complete if at least 10 h of meditation is done (both during class and at home), i.e., at least 6 sessions out of 9 are attended.

Biomarkers of compliance will be evaluated in a random sample of 30% of participants among the three arms of interventions, before and after the intervention: biomarkers of compliance with the nutrition program including (i) urinary total polyphenol excretion (adhesion to overall MedDiet pattern), (ii) urinary hydrohytyrosol concentration (compliance of extra-virgin oil), (iii) plasma alpha-linoleic acid concentration (compliance of walnuts), and (iv) biomarkers related to stress (steroid axis) will be evaluated by means of determination of cortisol in maternal 24-h urine [42].

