**Fig. 1 Fig1:**
[figure not shown]
Flow chart of participants in the randomized controlled trial. FGR, fetal growth restriction; RCOG, Royal College of Obstetrics and Gynaecologists; MBSR, mindfulness-based stress reduction; APO, adverse perinatal outcome; PE, preeclampsia

**Table 1 Tab1:** Study timeline

	Enrolment	Allocation	Post-allocation								Close-up
***Time point***	***Pregnancy***	***Pregnancy***	***Pregnancy***				***Delivery***	***Postpartum***			***Postpartum***
	*19–23.6 weeks*	*19–23.6 weeks*	*21–24.6 weeks*	*24–36 weeks*	*34–36.6 weeks*	*36–38 weeks*		*1–3 months*	*12 months*	*24 months*	*24 months*
	Screening visit	Randomization visit	Initial visit	Interventions	Final visit	Extra visit		Postnatal follow-up			

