**Enrollment:**											
Eligibility screen	√										
Informed consent		√									
Allocation		√									

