**Assessments:**											
Baseline variables											
Sociodemographic data			√								
Medical history			√		√						
Maternal life-style assessment			√		√			√		√	
Maternal nutritional assessment			√		√						
Outcome variables											
Primary outcome							√				
Perinatal outcomes							√	√			
Infant Bayley-III										√	√
Infant cardiovascular assessment										√	√
Other variables											
*Biological samples:*											
Maternal biological samples			√		√			√		√	
Feto-placental biological samples							√				
Infant biological samples								√		√	
*Maternal and fetal imaging:*											
Feto-placental US assessment					√						
EFW and feto-placental Doppler					√						
Fetal echocardiography					√						
Fetal neurosonography					√						
Maternal and fetal magnetic resonance rimaging						√					
*Infant extra tests:*											
Infant NBAS								√			
Infant ASQ									√		

*MedDiet* Mediterranean diet, *MBSR* mindfulness-based stress reduction, *US* ultrasound, *EFW* estimated fetal weight, *NBAS* Neonatal Behavioral Assessment Scale, *ASQ* Ages and Stages Questionnaires

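### The text takes the baseline questionnaires, diet score and maternal samples at enrolment, but Table 1 takes them at a post-allocation visit, so it is unclear whether they precede disclosure of the arm

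*Protocol article*

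**What the plan says.** Two places put the baseline measures at enrolment. The section on assessment and collection of outcomes (18a) opens "At the moment of enrollment (19.0–23.6 weeks of gestation), lifestyle questionnaires" and lists anxiety, perceived stress, well-being, mindfulness and sleep scales, a dietitian's assessment that includes MedDiet adherence, and maternal samples. The abstract's Methods paragraph agrees: clinical data, samples and lifestyle questionnaires "will be collected at enrollment and at the end of the interventions".

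Table 1 differs. Its columns run from a screening visit (Enrolment) to a "Randomization visit" (Allocation), both at 19–23.6 weeks, and then to an Initial visit at 21–24.6 weeks, the first column under Post-allocation. "Informed consent" and allocation are both ticked at the randomisation visit. The rows "Maternal life-style assessment", "Maternal nutritional assessment" and maternal biological samples have their first tick at the Initial visit.

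Allocation is open. Under Concealment mechanism (16b) the assignment is printed and "A copy will be given to the patient". Under Implementation (16c) the allocating investigator tells the woman her arm, and section 17a says that participants are not blinded.

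The initial diet score has a defined use. Under Participant compliance (11c), nutrition adherence is a gain of at least 3 points in the "total final score of the 17-item dietary screener compared to their total initial score". The per-protocol definition in section 20a uses the same 3-point change to exclude women in the nutrition arm.

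**The concern.** In an open-label trial of behaviour change, a self-reported baseline is most useful when it is recorded before the participant knows her arm. A woman who has just learned that she will be taught the Mediterranean diet may start to change what she eats, or may describe her diet differently. The same holds for stress, well-being and mindfulness scales in a woman told that she will, or will not, attend the mindfulness programme. Samples are less open to reporting effects but can still reflect behaviour that has already changed.

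If the initial value is taken after disclosure, it is a post-randomisation variable. A change measured from it then no longer describes change from the pre-allocation state. For the MedDiet score this matters in a concrete way, because the change decides who is counted as adherent and who stays in the nutrition arm's per-protocol population. That population is the planned robustness check on the primary outcome.

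**Working it through.** No sample size, power or alpha figure enters this point. The check compares visit labels and gestational windows.

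**1. Which visit.**

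| Measure | Section 18a and abstract | Table 1, first tick | Ticks under Enrolment or Allocation |
|---|---|---|---|
| Lifestyle questionnaires | enrolment | Initial visit (Post-allocation) | 0 |
| Dietitian's assessment, MedDiet score (18a only) | enrolment | Initial visit (Post-allocation) | 0 |
| Maternal samples | enrolment | Initial visit (Post-allocation) | 0 |

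This is unlikely to be a column shift from reading the PDF. Eligibility (screening), consent and allocation (randomisation visit) and the primary outcome (delivery) all fall where expected in the same table.

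**2. Which window.** Assumption: 23.6 means 23 weeks and 6 days, and 19, 21 and 24 mean 19.0, 21.0 and 24.0. Days = 7 × weeks + days.

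- Text window, 19.0–23.6: 7 × 19 = day 133 to 7 × 23 + 6 = day 167, which is 35 days inclusive.
- Initial visit, 21.0–24.6: 7 × 21 = day 147 to 7 × 24 + 6 = day 174, which is 28 days inclusive.
- Overlap: days 147 to 167, which is 21 days inclusive.
- Text window before the Initial visit opens: 147 − 133 = 14 days.
- Initial visit after the text window closes: days 168 to 174, which is 7 days. Table 1 starts the interventions at 24 weeks (day 168), so this week lies inside the intervention period.

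**3. Gap from allocation to baseline if Table 1 is followed.**

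- Largest: 174 − 133 = 41 days (5 weeks and 6 days).
- Smallest for a woman randomised at 19.0 weeks: 147 − 133 = 14 days.
- Smallest for a woman randomised at 21.0 weeks or later: 0 days, because the two windows overlap.

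**4. Does she know her arm by then?** Recruitment (15) goes directly from consent to randomisation and names no assessment between them. Sections 16b, 16c and 17a then have her told, given a printed copy and not blinded. No section says that the baseline measures precede disclosure.

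**5. Effect on the 3-point rule.** Let s be the shift in the initial score caused by knowing the arm. To be classed as adherent, a woman needs a gain of 3 + s points over her pre-allocation score. The documents give no value for s. Taking −1 to +1 as an illustrative assumption:

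- s = +1 (early improvement): 3 + 1 = 4 points needed.
- s = 0: 3 points needed.
- s = −1 (initial under-reporting): 3 − 1 = 2 points needed.

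The two directions oppose each other, so this shows that classification is sensitive to the shift and does not show a net bias.

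**The case against.** The strongest reply is that little in the trial depends on these measures. The primary outcome is birth weight below the 10th centile. The secondary outcomes are adverse perinatal outcome, Bayley-III, and infant blood pressure and heart rate. None uses a baseline questionnaire, diet score or sample. The main analysis is a logistic regression in the mITT population, and the article names no stress or diet covariate. The change score excludes women in one arm only, because mindfulness compliance in the per-protocol definition rests on attendance. The per-protocol analysis is itself only a robustness check. Most of the Initial visit window (21.0–23.6 weeks) precedes the intervention, and the gap may be zero. All of this stands and sets the limits of the point.

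The contradiction remains. A condensed article may leave detail out, but here two statements conflict on both visit and window.

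A reader might go further and infer that women's baselines are in fact recorded after they know their arm. The documents do not establish this. It follows only if Table 1 is the schedule used, and section 18a does not say whether enrolment ends before or after allocation. A reader might also infer that baseline-adjusted analyses are biased, or that women lost before the Initial visit damage the main result. The article describes no such adjustment, and the primary analysis needs no baseline value.

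**Conclusion.** The inconsistency holds. Section 18a and the abstract place these measures at enrolment (19.0–23.6 weeks in 18a). Table 1 places them at a post-allocation visit at 21–24.6 weeks.

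If Table 1 is followed, they are taken 0 to 41 days after an open allocation, and up to the last 7 days of the window fall within the intervention period. These figures rest on reading the notation as weeks and days.

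The reach is limited to three things:

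- the initial MedDiet score, used for nutrition-arm adherence and per-protocol exclusion;
- the before/after compliance biomarkers, measured in a random 30% of participants;
- change in self-reported stress and well-being, for which the article specifies no formal between-arm test.

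The primary mITT analysis is not affected. The size and net direction of any shift in the initial scores are unknown. The point is worth correcting because the per-protocol result is meant to test the robustness of the primary finding, and the correction is cheap.

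**What to change.** Reconcile section 18a, the abstract and Table 1 to one visit and one window, and state whether the baseline measures precede disclosure of the arm. Complete the questionnaires, dietary screener and maternal samples after consent and before the allocation code is released, and move their ticks in Table 1 accordingly. This adds no new measurement. The cost is a longer pre-allocation visit or a slightly later allocation.

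Recruitment began in February 2017 and follow-up was due to end in March 2022, so re-ordering helps only women still to be enrolled. If the baselines were in practice taken before disclosure, correcting Table 1 is enough. For women already randomised under the Table 1 order, treat changes from the initial value as post-randomisation measures and report the nutrition-arm per-protocol result with that limitation stated. This costs a few sentences in the analysis plan and the report.

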#### Plans to promote participant retention and complete follow-up {18b}

Research nurses involved in the study will follow-up participants in order to improve their compliance and will conduct the postnatal follow-up.

#### Data management {19}

Participants’ data for this study will be anonymized and entered into an electronic case report form. Investigators will collect maternal sociodemographic and clinical data. The electronic records will be only accessible to members of the research team with limited access through the username and password of authorized personnel. Researchers who access this database will be responsible for the confidentiality of the data collected. Data will be accessed only for statistical processing at given intervals, by professional statisticians with no access to the personal information of the study subjects.

#### Confidentiality {27}

All medical information is recorded on the hospital server. No data will be externally available. All data of this trial will be anonymized.

#### Plans for collection, laboratory evaluation, and storage of biological specimens for genetic or molecular analysis in this trial/future use {33}

Biological samples will be processed after collection and stored in −80°C freezers at Hospital Clinic-IDIBAPS Biobank. All samples for specimen banking are stored in coded tubes without any other attached information that would allow identification of the individual from whom the sample is collected.

### Statistical methods

#### Statistical methods for primary and secondary outcomes {20a}

The statistical analysis will follow the general regulatory recommendations given in the ICHE9 Clinical Trials guidelines [53].

The inferential analysis for the main variable (proportion of newborns with a BW below the 10th centile) will be performed by means of OR using a logistic regression model, with a 95% IC. The method of Hochberg will be used for the adjusted *p* values for the comparison of each interventional arm vs. control, i.e., the result *p* values of two comparisons will be ordered descending; the following decisions about the positive results of the study will be considered:
If the highest *p* value will be lowest than the threshold (0.0490), the study is positive for the two interventional arms vs. control.If the highest *p* value will be higher than the threshold (0.0490), the study is not positive for this, and the next variable *p* value should be lowest than the 0.0245 (0.0490/2) to be able to conclude the positive comparison of this interventional arm vs. control.

The specific analysis will be as follows:
Modified intention-to-treat population (mITT), defined as all randomized patients with neonates who did not end with a congenital malformation, diagnosed during pregnancy or in the postnatal period.Population per-protocol (PP), defined as all subjects included in mITT that participated in at least one visit without protocol deviation that might impact the study’s main assessments. The protocol deviation considered in this study is the low compliance with treatments. The next compliance criteria will be a reason for exclusion:
MBSR group: the patient attends less than 6 of 9 sessions (<67%).Nutrition group: the patient has a MedDiet score at final assessment <3 from the initial score.

The patient who withdrew informed consent will be excluded from all populations.

The main study analysis will be performed using the mITT, pre-randomization and baseline analyses, and primary and secondary efficacy analyses. The primary outcome analysis will also be performed using also ITT population as a supportive, PP population to test the robustness of the results.

No inferential analysis will be performed for the baseline comparability.

The SAS System3 (Release 9.4 or an upgraded version) or R version 3.5.2 (or upgrade version) will be used to analyze the datasets. Details for the statistical analyses are available in the statistical analysis plan, made by the external statisticians.

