### Outcomes {12}

#### Primary outcome

The primary outcome will be the prevalence of FGR at birth, defined as newborns with a BW below the 10th centile [43] according to local standards [44].

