#### Secondary outcomes

The following are the secondary outcomes:
(i)APO is defined as any of the following outcomes: (a) preterm birth, delivery <37 weeks’ gestation; (b) preeclampsia, defined as systolic blood pressure (SBP) ≥ 140 mmHg or diastolic blood pressure (DBP) ≥ 90mmHg at least 4 h apart after 20 weeks of gestation and proteinuria of ≥300 mg in 24 h; (c) perinatal mortality, fetal or neonatal mortality (within 28 days of life); (d) severe FGR, BW <3rd centile; (e) metabolic acidosis, an umbilical artery pH below 7.10 and/or base excess >12 mEq/L in the new-born and/or an Apgar score at 5 min below 7.0 assigned by the attending neonatologist or midwife; and (f) major neonatal morbidity in the presence of any of the following: intraventricular hemorrhage grade III/IV, necrotizing enterocolitis, periventricular leukomalacia, sepsis, bronchopulmonary dysplasia, and hypoxic-ischemic encephalopathy.(ii)Bayley-III score at 2 years of corrected postnatal age will be evaluated by means of their four items score (raw and scaled): (a) cognitive, (b) language, (c) motor, and (d) socio-emotional.(iii)The cardiovascular system at 2 years of corrected postnatal age will be evaluated by (a) SBP, (b) DBP, (c) mean arterial pressure, and (d) heart rate.

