### Methods in analysis to handle protocol non-adherence and any statistical methods to handle missing data {20c}

The handling of missing data will follow the principles specified in the ICHE9 [53] and the CPMP/EWP/1776/99. Guideline on Missing Data in confirmatory trials [54].

Formal imputations will be only performed for the main variable (proportion of newborns with a BW <10th centile) where missing data will be imputed by the following two strategies:
The main missing imputation strategy: the worst case will be imputed for all causes of missing data, i.e., BW < 10th centile.The secondary missing imputation strategy: multiple imputation with the observed rates in the control group in all cases.

The main analysis will be considered the worst-case imputation and the multiple imputation will be a sensitivity analysis.

For the remaining efficacy variables, no formal imputation will be performed, and the available data-only approach will be used. For the continuous efficacy variables, since the predefined approach mixed models for repeated measurements [55–57] is robust to assess the presence of missing at random, the analysis will be done with all subjects despite the presence of missing data. Of note, this method calculates the estimations based on the variance-covariance structure but without any formal imputations.

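### Read literally, the main analysis set leaves out pregnancies that end in fetal death, although fetal death is an APO event and the primary outcome has a worst-case rule; the wording does not settle which reading applies

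*Protocol article*

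**What the plan says.** Section {20a} of the protocol article (Statistical methods for primary and secondary outcomes) defines the mITT as "defined as all randomized patients with neonates who did not end with a congenital malformation, diagnosed during pregnancy or in the postnatal period". It then gives this set its role: "The main study analysis will be performed using the mITT, pre-randomization and baseline analyses, and primary and secondary efficacy analyses". The per-protocol set is a subset of the mITT and inherits its membership. The ITT population has a limited role: "The primary outcome analysis will also be performed using also ITT population as a supportive, PP population to test the robustness of the results". The only other removal stated for all sets is withdrawal of consent.

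Three other rules bear on fetal death:

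- **Secondary outcomes**, APO component (c): "perinatal mortality, fetal or neonatal mortality (within 28 days of life".
- **Primary outcome**: "defined as newborns with a BW below the 10th centile [43] according to local standards [44".
- **Section {20c}**, main strategy for missing primary data: "the worst case will be imputed for all causes of missing data, i.e., BW < 10th centile". Other efficacy variables, APO among them, are analysed on available data without imputation.

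The article does not say that fetal deaths are excluded from the mITT, and it does not say that they are kept.

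**The concern.** Women are randomised from 19 weeks, so some pregnancies may end in late miscarriage or stillbirth after allocation. Having a neonate is therefore a condition met, or not, after randomisation. A main analysis set that requires it compares the arms among survivors of the pregnancy, and randomisation no longer protects that comparison.

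Fetal death is also not incidental here. Section {6a} puts it first among the poor outcomes of small fetuses, and APO counts it as an event. If fetal deaths leave the set in which APO is analysed, an arm with more of them loses those events from its count. APO is a secondary endpoint, but section {14} uses it to set the sample size. The trial is open-label (section {17a}), so a choice of reading made late could be made with allocation known.

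**Working it through.** **1. The passages side by side, on the literal reading.**

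| Rule | What it requires for a fetal death | What the literal mITT does |
|---|---|---|
| APO component (c) | counted as an event | woman is not in the set, so the fetal part of the component is not seen |
| Worst-case rule in {20c}, primary outcome | failure if birth weight is missing, whatever the cause | woman is not in the set, so nothing is imputed |
| ITT analysis in {20a} | presumably includes her | stated for the primary outcome only, as supportive |

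If the set instead excludes malformations only, both of the first two rules work as written.

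**2. The plan's own figures.** 3 × 406 = 1218 and 3 × 367 = 1101 agree with section {14}. The control rates behind 406 and 367 are not given, so the per-arm sizes cannot be confirmed. With a pooled two-proportion formula, two-sided 5%, 80% power and no dropout, 406 per arm fits a control APO rate of about 10.65% (for a 50% reduction) and 367 per arm fits a control FGR rate of 30.0% (for a 30% reduction). Other choices of alpha, sidedness, continuity correction and dropout (0% or 10%) fit APO rates from 8.55% to 15.0%. The point does not depend on these rates; they only guide the illustration.

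**3. Effect on APO.** Inputs: 406 per arm (section {14}); the 50% reduction (section {14}); control APO of 10%, with 12% as a check (assumed); fetal death rates of 0.5% to 1.5% (assumed). Let p be the APO risk with fetal deaths counted and f the fetal death rate, with subscript C for control and T for intervention. Each fetal death is one woman with APO, so removing her takes one from numerator and denominator:

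p* = (p − f) / (1 − f), and RR* = p*_T / p*_C.

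| f control / f intervention | Women removed (406 × f) | p* control | p* intervention | RR* (RR with deaths counted = 0.50) | RR* at 12% vs 6% |
|---|---|---|---|---|---|
| 1% / 1% | 4 / 4 | 0.090/0.990 = 9.09% | 0.040/0.990 = 4.04% | 0.44 | 0.455 |
| 0.5% / 1.5% | 2 / 6 | 0.095/0.995 = 9.55% | 0.035/0.985 = 3.55% | 0.37 | 0.395 |
| 1% / 0.5% | 4 / 2 | 0.090/0.990 = 9.09% | 0.045/0.995 = 4.52% | 0.497 | 0.497 |
| 1.5% / 0.5% | 6 / 2 | 0.085/0.985 = 8.63% | 0.045/0.995 = 4.52% | 0.52 | 0.055/0.995 ÷ 0.105/0.985 = 0.52 |

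The direction depends, approximately, on whether the ratio of fetal deaths (intervention to control) is above or below the APO risk ratio. Above it, exclusion exaggerates the benefit (rows 1 and 2). Equal to it, little changes (row 3). Below it, exclusion understates the benefit (row 4). In row 2 the intervention arm has three times the fetal deaths and looks better for it.

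**4. Effect on the primary outcome.** Assume FGR of 30% vs 21% among births with a birth weight, which is RR 0.70 if fetal deaths are left out. If all are counted as failures, the rate is q = f + (1 − f)p:

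- 1% in each arm: 0.01 + 0.99 × 0.30 = 30.7%; 0.01 + 0.99 × 0.21 = 21.8%; RR 0.71.
- 0.5% vs 1.5%: 0.005 + 0.995 × 0.30 = 30.35%; 0.015 + 0.985 × 0.21 = 22.2%; RR 0.73.

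The planned effect measure is the odds ratio; risk ratios are used here only because they are easier to read.

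**The case against.** The strongest reply is that the sentence is about malformation and nothing else. It speaks of diagnosis during pregnancy, which suggests that the term for the infant is used loosely for fetus or infant, and section {10} has the same pair of exclusions, prenatal anomalies and abnormalities found after birth. Withdrawal of consent is the only other removal spelled out. On that reading fetal deaths stay in, and the rules for APO and missing data make sense. The reading is tenable, so a reader who infers that the plan does exclude fetal deaths goes further than the text. It is not established either: a liveborn child can have a malformation that was found prenatally, and elsewhere (section {10} and APO component (c)) the article keeps fetal and neonatal apart.

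Some stronger inferences fail:

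- A reader might conclude that the mortality component of APO could only ever be zero. Neonatal deaths up to 28 days would still count.
- A reader might conclude that every fetal death breaks the worst-case rule. A stillborn infant may have a recorded weight, so the value is not always missing, and the rule covers the primary outcome only.
- A reader might fear that a real benefit on the primary outcome would look like harm. The calculation does not show this: the risk ratio stays between 0.70 and 0.73, and the supportive ITT analysis partly covers that endpoint.

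It is also fair that secondary tests are called exploratory (section {20b}) and that the article refers to a separate analysis plan for detail. That lowers the weight of the point without removing it. The article states the definition of its main set, and that definition, as worded, conflicts with its own endpoint. If the analysis plan is clearer, the two texts still need to agree.

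**Conclusion.** The point holds as an unresolved ambiguity in the main analysis set whose literal reading contradicts two other rules. It does not hold as a demonstrated exclusion.

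On the literal reading, APO would be compared conditional on fetal survival, with no stated ITT analysis to set beside it, and the bias can go either way. In the cases worked, the APO risk ratio of 0.50 becomes anything from 0.37 to 0.52. The effect on the primary risk ratio is small.

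The fetal death rates and the outcome rates are assumptions, because the article gives none. The size of the effect therefore illustrates what could happen and does not estimate it. The conflict between the passages does not rest on those rates.

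**What to change.** Reword the mITT in {20a} as all randomised women except those whose fetus or infant has a congenital malformation, and those who withdrew consent, whether or not the pregnancy ends in a live birth. State that every fetal death counts as an APO event. State for the primary outcome that a fetal death without a classifiable birth weight falls under the existing worst-case rule in {20c}. Bring the statistical analysis plan into line, and settle the wording before outcomes are examined by arm.

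The cost is a few sentences. Birth weight and perinatal mortality are already collected, and neither the sample size nor the planned tests change.
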